## Abstract

**Introduction:**

Mistreatment, discrimination, and poor psycho-social support during childbirth at health facilities are common in lower- and middle-income countries. Despite a policy directive from the World Health Organisation (WHO), no operational model exists that effectively demonstrates incorporation of these guidelines in routine facility-based maternity services. This early-phase implementation research aims to develop, implement, and test the feasibility of a service-delivery strategy to promote the culture of supportive and dignified maternity care (SDMC) at public health facilities.

**Methods:**

Guided by human-centred design approach, the implementation of this study will be divided into two phases: development of intervention, and implementing and testing feasibility. The service-delivery intervention will be co-created along with relevant stakeholders and informed by contextual evidence that is generated through formative research. It will include capacity-building of maternity teams, and the improvement of governance and accountability mechanisms within public health facilities. The technical content will be primarily based on WHO’s intrapartum care guidelines and mental health Gap Action Programme (mhGAP) materials. A mixed-method, pre-post design will be used for feasibility assessment. The intervention will be implemented at six secondary-level healthcare facilities in two districts of southern Sindh, Pakistan. Data from multiple sources will be collected before, during and after the implementation of the intervention. We will assess the coverage of the intervention, challenges faced, and changes in maternity teams’ understanding and attitude towards SDMC. Additionally, women’s maternity experiences and psycho-social well-being—will inform the success of the intervention.

**Expected outcomes:**

Evidence from this implementation research will enhance understanding of health systems challenges and opportunities around SDMC. A key output from this research will be the SDMC service-delivery package, comprising a comprehensive training package (on inclusive, supportive and dignified maternity care) and a field tested strategy to ensure implementation of recommended practices in routine, facility-based maternity care. Adaptation, Implementation and evaluation of SDMC package in diverse setting will be way forward. The study has been registered with clinicaltrials.gov (Registration number: NCT05146518).

## Introduction

The experience of childbirth can change a woman’s life and leave lasting memories [1, 2]. Up to a third of women appraise their experience of giving birth as traumatic [3]. These psychological distresses during labour leaves them vulnerable to the care processes in health facilities such as unfamiliar personnel, medicalised procedures and other conditions [4]. Regardless of it, women around the globe, particularly in low- and middle-income countries (LMICs) are mistreated and rarely offered psychosocial support during childbirth at health facilities [5]. Such poor encounters may have adverse effects on the quality and outcome of birthing experiences, which could lead to psychological disorders [6–9], and may deter women from seeking health care in the future [10]. Additionally, range of other socio-economic (e.g. poverty) and health-related (e.g. anxiety, depression or disability) vulnerabilities predispose women to discriminatory care which may further aggravate the situation, leading to more intense sufferings [11].

Respectful Maternity Care (RMC) not only reduces the need for superfluous medical intervention but also strengthens psychosocial processes, thus improves birth outcomes and maternal well-being [4]. In the year 2014, the World Health Organisation (WHO) issued a policy statement that “every woman has the right to the highest attainable standard of health, which includes the right to dignified, respectful health care” [12]. Subsequently, they released a revised framework for quality of maternal and newborn healthcare that put special emphasis on women’s experience of care (dignity, effective community and emotional support) [13], followed by another framework to aid understanding of different forms mistreatments encountered by women during childbirth [5]. More recently, WHO released a comprehensive set of evidence-based policy recommendations to promote women’s experiences of intrapartum care [14]. These policy directives from the WHO indicate the need for integrated health services that should not only respect women’s dignity but also fulfil their emotional or psychosocial needs during maternity care [12]. This proposition presents with an opportunity to link WHO’s Mental Health Gap Action Programme (mhGAP) materials in addressing psychosocial needs of pregnant women by bringing a positive change in the maternity care settings, as per newly set WHO standards for intrapartum care [14].

However, despite the release of these guidelines, no operational model exists that effectively demonstrates incorporation of these principles in routine facility-based maternity services [15]. Strategies applied thus far have not been adequately embedded in health systems. While these approaches might appear effective, information about them is relatively sparse, and their overall evidence is rated with low certainity for risk of bias for all outcomes [15]. Moreover, these interventions have suffered from numerous challenges around acceptability and feasibility, particularly in low-resource settings where the health system was plagued with issues of governance and accountability, and mistreament of women was considered socially acceptable [10, 16]. It is therefore recommended that, in order to achieve greater feasibility, acceptability and impact, the design and development of such interventions should use a participatory approach, while taking into account the socio-cultural context and the health system’s environment and constraints [16].

Keeping in view of the complexity of the issue, translation of WHO’s policies and guidelines into practice necessitates the use of implementation research to inform design and implementation of contextually-appropriate interventions, and embedding them within the healthcare system in a sustainable manner. Following Medical Research Council framework, we propose early-phase implementation research to develop, implement and test feasibility of a service delivery intervention package before running a full-scale trial [17].

### Aim and objectives

The overall aim of this research is to support inclusive, supportive and dignified maternity care within health systems, especially from the perspective of a) capacity of service providers, and b) accountability and governance (see Fig 1 for definition of key concepts). The specific objectives are:

a) Design a contextually-informed (or evidence-based) service-delivery model through a participatory, consensus-driven process for inclusive, supportive and dignified maternity care; andb) Implement and test the feasibility of the intervention model for its content and operationalisation in public health facilities

**Fig 1 pone.0263635.g001:**
[figure not shown]
Operational definitions of key concepts [14, 18] a[19].

## Methods

### Country context

This early-phase study will be conducted in Pakistan which has one of highest rates of maternal mortality [20], and is ranked the riskiest country for newborns [21]. The country also has the highest prevalence (range 29–66%) of anxiety and depression among women in Asia [22]. Healthcare in Pakistan is delivered through a three-tiered health system: primary, secondary and tertiary. The proposed research focuses on secondary-level healthcare where inpatient childbirth facilities are formally introduced through maternity ward and labour room services. Specialist consultation and hospital admissions fall into this category. It includes two types of health facilities: district (District health quarter Hospitals–DHQ) and sub-district level (Tehsil Head Quarter—THQs). Recent evidence from secondary-level health facilities revealed high reports (97%) of disrespectful and abusive intrapartum care in health facilities, including a violation of women’s right to information (70%); lack of consensual (78%) and confidential care (69%); lack of supportive care; loss of women’s autonomy; and verbal and physical abuse [23]. The proportion of total births that takes place in public health facilities is startlingly low at (15%) [24]. Numerous factors in the running of health systems contribute to this compromised care, among them: lack of awareness and professional capacity of service providers around respectful and supportive care; a non-conducive work environment; and poor governance and accountability [25].

### Intervention

It will be a theory-driven, inclusive service-delivery package which will be developed using the principles of the human-centred design approach. The model will include capacity-building of maternity teams, and the improvement of governance and accountability mechanisms within public health facilities to ensure that all women are treated with compassion and dignity, while also catering for their diverse needs, including disabilities and common mental health conditions. The integration of psychosocial support in routine maternity care will be a unique feature of the intervention package, a principal aim of which is to address the psychological needs of birthing women and their companions. The technical content of the SDMC training handbook will be based on two integrated modules: WHO’s intrapartum care guidelines [14] and Mental Health Gap Action Programme (mhGAP) training [26] and implementation guidelines [27]. As part of the SDMC package, maternity staff will have job-aids for referencing of essential SDMC behaviours, steps of providing psychosocial support, and reassuring maternity patients about their rights and responsibilities.

Operationally, the core components of intervention would include: capacity-building of a typical maternity team comprising clinical staff (gynaecologists, doctors, nurses) and support staff (ward boys/porters and maids); collaborative care, a team-driven approach, led by gynaecologists (ward in-charge), attempts to integrate care and behaviour practices of staff according to the principles of measurement-guided care-plans, quality improvement and accountability, with a focus on meeting SDMC needs; staff and patient feedback: a complaints register will be maintained by designated staff; and brief exit interviews will elicit, and record, the degree to which care has been supportive and respectful; Accountability and governance (performance review): reports of non-respectful care will be discussed, and remedial actions decided, in periodic meetings.

### Theory of change

The intervention development will be guided by the COM-B (’capability’, ’opportunity’, ’motivation’ and ’behaviour’) framework. Conceptually, the intervention will aim to improve *capability* of care providers to provide supportive and dignified care by providing relevant knowledge and skills, *opportunity* to enact such behaviours by altering changes in the systems and inculcating the use of collaborative care approach, and *motivation* by re-enforcing the benefits of inclusive care on individual, health systems, and community [28].

It is hypothesised that building capacity for collborative care, improving maternal orientation, and embedding review and accountability mechanisms in health facilities will enable service providers and staff to provide supportive and dignified maternity care. This will lead to improvement in health systems’ overall responsiveness towards psychosocial needs of women and ensuring women’s dignity is respected (see Fig 2 for logic model).

**Fig 2 pone.0263635.g002:**
[figure not shown]
Logic model of the research.

### Study phases

#### Implementation phases

The implementation of this study will be divided into two phases: (1) Development of intervention: grounded in formative research around supportive and dignified care, participatory approach will be used to co-create service-delivery intervention package; and (2) Implementing and testing feasibility: a two-level feasibility assessment will be carried out–health systems and staff assessment, and women’s experiences around SDMC.

We will use the framework of human-centred design (HCD) to guide implementation of this study (see Fig 3). Human-centred design is an emerging concept and being used increasingly in global health [29]. The approach is classified in three phases: inspiration, ideation, and implementation and testing.

**Fig 3 pone.0263635.g003:**
[figure not shown]
Stages of SDMC intervention development, implementation and feasibility testing.

### Objective 1—Design a contextually-informed (or evidence-based) service-delivery model through a participatory, consensus-driven process for inclusive, supportive and dignified maternity care

#### Phase 1: Inspiration

The first step is empathise–whereby, through a formative research we will understand prevalent behaviours, challenges and opportunities around SDMC. It will be supplemented by review of national and international guidelines, and best practices around the topic in focus. We will begin with the participatory approach to engage with key stakeholders, including practitioners, programme managers, policy makers, and community representatives to ensure contribution and ownership of the project.

#### Formative research

*Focus Group Discussions (FGDs)*. A total of five to eight FGDs will be conducted with postpartum women who have delivered in public health facility during the last three months. These women will be identified from a list frame to be obtained from the selected health facility. The FGDs will broadly explore: (a) attitudes towards facility-based births; (b) motivations to give birth at the facility; (c) expectations regarding maternity care; and (d) perceived quality of care with according to the Hulton framework for quality of care in maternity services [30]. The framework focuses on both ‘provision of care’ and ‘experience of care’ (human and physical resources, cognitive support, respect and dignity, equity, emotional support). A trained sociologist/anthropologist will conduct FGDs who will be accompanied by note-taker. Informed consent will be taken from participants of FGDs and all discussions will be audio-recorded. The data generated from FGD will inform development of SDMC intervention package and contextualised structured tools to assess experiences of SDMC at healthcare facilities.

*Health facility assessment*. The assessment of health facility will comprise of: a) interviews with health system staff (clinical and non-clinical service providers and administrators) and b) review of management information system.

***Indepth interviews (IDIs) with staff*:** IDIs will be conducted with clinical and non-clinical maternity staff and administrators to broadly understand challenges and opportunities around SDMC. More specificially, our themes would include: routine operations of maternity section, governance and accountability mechanisms around SDMC; knowledge, attitude and motivation towards SDMC; and experiences of patient interactions. Additionally, we will explore their perceptions about working conditions, job responsibilities, empathy with and prejudice against patients, and relationship with co-workers and supervisors. Preliminary information about health management information system will also be collected during these interviews and will be systematically assessed in observation visits. The COM-B behavioural framework will guide the the development of interview guide and data synthesis to understand individual and systemic factors around motivation, capabilities and opportunities for supportive and dignified maternity care.

*Observations*.

***Review of management information system (MIS)*:** We will review the kind of information documented on inpatient records and assess mechanisms to use this data to make informed decisions. Understanding MIS will enable the investigators to create or strenthen mechanism for record keeping on incidents of any mistreatment as a measure of accountability.

#### Review of relevant national and international material

We will conduct a thorough review of existing national and international material that is pertinent to the supportive and dignified maternity care. This would broadly include: existing national service delivery guidelines for maternity care during labour and childbirth; WHO recommendations for intrapartum care; mhGAP material for neurological disorders and substance abuse; existing training material on respectful maternity care.

#### Phase 2: Ideation

In second phase, data synthesis will generate numerous issues and their possible solutions around supportive and dignified maternity care. These solutions/ideas will then be discussed with stakeholders to select the ones that are most relevant and applicable in the given context, around which the prototype will be formally developed. The prototype will undergo provisional testing through a collective review with stakeholders–who will reflect on its relevance and operational feasibility in their routine practice. The prototype will then be revised based on feedback and learnings accordingly. If the agreed solutions do not seem to be viable, the new sets of ideas will be explored altogether from data and in brainstorming sessions with stakeholders. This will be iterative process will run till the group reaches to a final consensus.

### Objective 2: Implement and test the feasibility of the intervention model for its content and operationalisation in public health facilities

#### Phase 3: Implementation and testing

The third phase of HCD fall within the scope of second study objective. In phase three, the finalisation of prototype will be followed by pilot testing in real-life settings over a period of three months. It is important to note that this implementation is will be considered pilot as the field learnings will be fed back into design of intervention package.

*Evaluation design*. A mixed-method, pre-post design will be used to test feasibility of the intervention prototype.

*Study settings*. The study will be implemented at six public health facilities–with three facilities in each Thatta and Sujawal districts of southern Sindh province, Pakistan. These contagious districts are located approximately 100 kilometres away from megacity, Karachi. Each district has a population of approximately 0.8 million inhabitants, with 82% of them residing in rural areas [31] and just over half (52.3%) of the population belong to the poorest wealth quintile relative to the Sindh province (South of Pakistan) [32]. Only 15.8% of the total births take place in public sector health facility [32].

*Study population*. The primary target-audiences will be women in childbirth and service providers (clinical and non-clinical staff) of the labour room / maternity wards.

#### Health system and staff assessments

*Quantitative methods*. Baseline assessment will follow the capacity-building of clinical and support staff of the health facility in training modules. The maternity team will receive comprehensive 3-day training on SDMC that is tailored to their contextual settings. Senior staff members will become master trainers, responsible for providing supportive supervision to ensure adherence to set standards. Feedback from staff will be sought during the training about the relevance of content and its implementation feasibility.

The knowledge and attitude of training participants (clinical and non-clinical staff and administrators) regarding SDMC will be assessed through pre-and post-training tests. The tools will be developed in accordance with the intervention package, after it is finalised.

*Qualitative methods*. During the intervention period quality audits (or supportive supervision visits) will be routinely conducted on all selected health facilities to assess adoption of, and adherence to, quality standards through observation of women-provider interactions, staff coordination, and facility assessments. The maternity staff will be provided with customised feedback based on the observation findings.

Post-intervention, in-depth interviews will be conducted with practioners and programme managers to explore intervention fidelity, dose and coverage, penetration of SDMC practices across cadre, and individual, interpersonal, and system-level facilitators and barriers that were encountered during delivery of the intervention in routine practice. We will also gather their suggestions for improvement in the SDMC intervention package.

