#### Women’s experiences

*Quantitative methods*. Pre-post intervention assessments will gather information on women’s experiences of SDMC at health facilities, and suffering of postpartum depression within 42 days of childbirth. Unlike health system assessment, two independent group of women will be enrolled in baseline and endline. Recently published structured questionnaire on mistreatment during childbirth will be contextually adapted and used for these pre-post assessments [33]. Postpartum depression and anxiety will be assesed using Patient Health Questionnaire– 9 and Generalised Anxiety Disorder– 7, respectively.

*Sample size calculation*. In order to get a sense of sample size requirement for a meaningful change study outcomes, the sample size was estimated with varied effect sizes. Mean score mistreatment was considered as key outcomes which is taken from a background study in similar setting that yielded a mean score of 25 (score range 0 to 40). A total of 308 postpartum women will be required to detect a statistical difference of 2.5-units decrease (or 10% reduction) in the mean score of mistreatment (from 25 [34] to 22.5) with standard deviation of 6 [34], 90% power, 5% level of significance, 2 design effect, and 10% lost-to-follow-up (LTFU) and/or non-response. We decided to proceed with a sample of 308 as it gives sufficient precision to perform range of additional analysis such as estimation of prevalence of different types of mistreatment and the effect of intervention on each of these types of mistreatment, while will not negatively affecting study timelines.

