*Sampling strategy*. A convenience sampling technique will be used for the selection of study participants. All women giving births at the selected hospitals during the data collection period will be invited to participate in the survey, until the desired sample is achieved. The volume of women attending each health facility for childbirth may vary; hence based on historical trends the sample size will be proportionally distributed across health facilities according to the caseload. During the consent process, participants will be informed and asked whether they would be interested in participating in a follow-up interview in their homes at six weeks of postpartum. Women who showed interest in home-based interview and gave consent will be recruited in the survey. Participants who lived outside of the study district or even in hard-to-reach rural areas of the district will be excluded from this sample due to logistical constraints.

*Data collection and management*. Standardised and contextually-adapted tools will be used in this study. All data collection tools will be translated in the relevant local language and pre-tested in similar settings prior to being used. Data collectors with prior experience will be hired and trained for baseline and endline assessments, and routine audits. In-depth interviews (IDIs) and focus group discussions (FGDs) will be conducted by trained sociologist and/or anthropologist. All data collectors will receive a comprehensive and standardised training on both theoretical and practical aspect of study instruments. In addition, data collectors will be trained on rapport building, research ethics, and interviewing techniques. Research Officer will conduct: shadow interviews (observation of data collection) and independent re-interview/assessment with a sub-sample to ensure data quality.

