The study protocol, the informed consent forms, and other appropriate documents will be submitted and approved as required by Ethics review committees of the Aga Khan University and Research Ethics Committee to London School of Hygiene and Tropical Medicine. All research staff will be trained in research ethics. The Principal Investigator (PI) at the research site will be responsible for ensuring that all requirements of the local ethics committee are met. Before implementing any changes to the protocol, informed consent, advertising, or participant written materials, the site PI will have the changes approved by the local ethics committees, except where necessary to eliminate immediate hazards to human participants.

*Status and study timelines*. This study will span over twenty four months. The first three months will involve planning, development of study protocol and draft of study questionnaires, obtaining ethical clearance, and hiring of project staff. The next four months will be used for formative research to inform the design and development of SDMC intervention. It will follow development of SDMC intervention and its implementation strategy through a consultative process with stakeholders over six months period. The finalization of intervention package will be followed by baseline assessment and training of service providers over two months. Intervention will run over a period of six months followed by three months of endline assessment, data analysis, writing, and dissemination.

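### The methods text places the baseline assessment after staff training, against the timeline and the pre-post design; the order needs correcting and the baseline group should be defined by date of birth

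*Protocol article*

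**What the plan says.** On the order of baseline and training, the protocol article says two things.

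- In the quantitative part of Health system and staff assessments, the text reads: "Baseline assessment will follow the capacity-building of clinical and support staff of the health facility in training modules". The next sentence describes the training itself: "The maternity team will receive comprehensive 3-day training on SDMC".
- Status and study timelines (under Key indicators): "The finalization of intervention package will be followed by baseline assessment and training of service providers over two months". Baseline is named first, and both activities share one two-month block.

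Other places presuppose a measurement before the intervention. The abstract promises: "Data from multiple sources will be collected before, during and after the implementation of the intervention". Evaluation design calls the study pre-post. The staff section plans knowledge and attitude tests before and after training. The Intervention section lists capacity-building among the core components.

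For the women's survey, the section Women's experiences says that "two independent group of women will be enrolled in baseline and endline". Enrolment takes place at birth: "All women giving births at the selected hospitals during the data collection period will be invited to participate in the survey", and it continues until the target number is reached. Women are then seen at a "follow-up interview in their homes at six weeks of postpartum". No sentence says how a baseline woman's date of birth-giving must relate to the first training day.

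**The concern.** A pre-post comparison needs a first round that has not met the intervention. Training the maternity team is the first active part of this intervention, so a baseline taken after it is not a pre-intervention measurement. If the sentence in the staff section governs the women's survey, or if enrolment of baseline births runs on past the training date, some or all first-round women are cared for by trained staff. The difference between rounds then leaves out part of the training effect and is biased toward no change.

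This comparison is the basis of the sample size calculation. It is the only service outcome in Table 1, and the abstract says it will inform the success of the intervention. A missed baseline cannot be collected later, so the order has to be settled before the first training day.

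**Working it through.** **1. The two orders side by side.** The staff section gives training, then baseline. The timeline gives baseline, then training, although it implies this only by the order of naming and does not say that baseline ends before training starts. Two readings of the staff sentence are possible:

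- It covers staff only. It then conflicts with the pre-training tests planned in the same section and with the paired tests under Data analysis, which compare staff before and after training.
- It covers the women's survey too. It then conflicts with the pre-post assessment of women and with the abstract.

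The sentence needs correction on either reading.

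**2. The plan's own timeline.** The blocks under Status and study timelines are planning 3, formative research 4, development 6, baseline and training 2, intervention 6, and endline and reporting 3 months: 3 + 4 + 6 + 2 + 6 + 3 = 24. The stated 24 months is reproduced exactly. (Phase 3 speaks of a three-month pilot, which would give 21. That is a separate discrepancy and does not alter the two-month block.)

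**3. Time left for baseline births, if six-week interviews must finish inside the two-month block.** The article does not state this condition.

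- Two months = 2 × 30.44 = 60.9 days. The interview lag is 6 × 7 = 42 days.
- Window = 60.9 − 42 = 18.9 days, or 2.7 weeks.
- With 59 to 62 days for two months, the window is 17 to 20 days; with eight weeks (56 days), 14 days.
- If the 3 training days must also come after the last interview, 59 to 62 days leave 14 to 17 days.

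**4. Enrolment rate implied.** The article gives a total of 308 without saying clearly whether this is both rounds together (154 each) or each round.

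- Over 2.7 weeks, 154 women need 154 / 2.7 ≈ 57 enrolled births a week (about 9.5 per facility), and 308 women need about 114 a week (about 19 per facility).
- If interviews may run on after the block and only the 3 training days are set aside, about 58 days (8.3 weeks) are available. The need falls to about 19 a week for 154 women and about 37 for 308.

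The article gives no caseload for the six facilities. A rough bound uses its population of 2 × 0.8 million and its 15.8% public-sector share, with an assumed 25 to 35 births per 1,000 people a year. The result is 1,600,000 × 0.025 × 0.158 / 52 ≈ 122 to 1,600,000 × 0.035 × 0.158 / 52 ≈ 170 births a week. That covers every public facility in both districts, before refusals and the exclusion of women in hard-to-reach areas. It does not show whether the six sites could meet the short window.

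**5. Size of the bias.** Let f be the share of baseline women who deliver after training, and s the share of the full effect that they already receive. The planned change is 22.5 − 25 = −2.5, so the expected observed change is −2.5 × (1 − f × s).

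- f = 0.3, s = 1: −2.5 × 0.7 = −1.75.
- f = 1, s = 0.5: −2.5 × 0.5 = −1.25.
- f = 1, s = 1: 0.

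The values of f and s are illustrations; the article gives neither.

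**The case against.** The strongest reply is that the sentence is a slip for the passive form, with baseline to be followed by training. The timeline uses the same verb in this inverted way when it moves from formative research to development, and every other statement in the article supports baseline first. The sentence also stands in the staff section, whereas the women's survey has its own section. Both arguments have weight: a slip is the likely explanation, and applying the sentence to women is an inference. They do not remove the error, because the sentence is wrong for staff as well and no separate timing is given for the women's survey.

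A reader might infer that the six-week lag itself exposes baseline women. It does not. Exposure is set by the date of birth relative to training, and a woman who delivered before training and is interviewed afterwards is still an unexposed respondent on her childbirth care. A reader might also infer from the short window that enrolment will overrun the training date. That depends on an unstated condition and an unknown caseload, so it remains a plausible pressure and not a demonstrated event.

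It is also fair to say that an article may leave a birth-date rule to the full protocol. Its absence alone would be no finding. What is open to criticism is a stated sequence that contradicts other stated text. Finally, the Discussion says that change in women's experiences is not the primary objective and that the study will not give robust evidence of effectiveness. That lowers the stakes but does not make a post-training baseline usable.

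**Conclusion.** The contradiction stands and should be corrected. Its harm is conditional. If the staff-section order is followed for the women's survey, or if baseline births are enrolled after training starts, the pre-post difference is pulled toward zero by the factor 1 − f × s. This can reach the whole planned 2.5 points only if all baseline births follow training and training carries the entire effect. The second assumption is strong, since the Intervention section lists other core components besides training.

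The article does not support the stronger conclusion that the comparison would be beyond repair. If only some baseline women delivered after training, their delivery dates identify them, because the interview is timed from delivery, and they can be excluded or analysed separately at the cost of numbers. Only a baseline made up entirely of post-training births could not be rescued.

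The figure of about 2 to 3 weeks for baseline births rests on interviews having to finish within the shared two-month block. It is a reason to state the rule clearly, and is not itself evidence of contamination.

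**What to change.** 1. Reword the sentence under Health system and staff assessments so that baseline comes before training, in line with the timeline.
2. Under Women's experiences, define the rounds by date of birth. Baseline women are those who gave birth before the first training day at that facility. Births between that day and the start of the intervention at the facility count in neither round.
3. State that six-week interviews of baseline women may run during or after training. This removes the pressure described in steps 3 and 4 of the working.

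The cost is small. The sample size does not change. Some births around training are not used, and enrolment of baseline births may have to begin somewhat earlier, which could reach into the end of the development period and needs fieldwork to be ready by then. Some depression and anxiety scores of baseline women would be collected while the intervention is running. This should be stated as a limitation, although the childbirth care those women report on would still be care before training.
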